### Interim analyses {21b}

The study will incorporate two strategically timed interim analyses to monitor trial progress and participant welfare. The first analysis, focused on safety monitoring, will be conducted after the initial cohort of 40 participants completes their mid-treatment assessments. This evaluation will systematically compare adverse event profiles between the online and in-person EMDR groups, with particular attention to clinically significant indicators such as dissociation rates. Should the analysis reveal substantially higher adverse events in either treatment arm—for instance, elevated dissociation occurrences in the online EMDR group—the protocol will be adaptively modified to incorporate additional stabilization sessions for affected participants while maintaining trial continuity.

The second interim analysis, designed to assess efficacy and futility thresholds, will occur when 60 participants (75% of the target sample) have completed their end-of-treatment evaluations. This analysis will employ O’Brien–Fleming statistical boundaries to determine whether the accumulating data demonstrates either compelling evidence of treatment success or insufficient likelihood of achieving meaningful results. For example, if the analysis reveals that online EMDR demonstrates near-equivalent efficacy to in-person delivery—as might be evidenced by merely a 0.5-point difference on the HAM-D-17 scale (*p* = 0.005)—the trial could be responsibly terminated early based on established efficacy. Conversely, should the data suggest minimal probability of ultimately proving non-inferiority, the futility provisions would be activated to conserve resources. These pre-specified analytical checkpoints are integrated into the study design to balance scientific rigor with ethical responsibility and operational efficiency.

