## Assignment of interventions: blinding

### Who will be blinded {17a}

Due to the single blind-nature of intervention, complete blinding is not feasible for clients or therapists regarding delivery mode (online vs. in-person EMDR). However, therapists will remain blind until after completing the initial consultation with clients. Outcome assessors (research assistants) and data analysts will maintain full blinding throughout the trial. To minimize bias:Outcome assessors will perform clinical evaluations before therapy sessions begin and without access to subsequent treatment setting information.Data analysts will work with de-identified datasets using group codes.For fidelity analysis, independent reviewers will assess edited audio/video recordings with all platform-specific references removed.Blinding success will be empirically evaluated at the study midpoint by asking blinded personnel to guess group allocations, with ≤ 60% correct guesses indicating adequate maintenance of blinding.

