### Composition of the data monitoring committee, its role, and reporting structure {21a}

The Independent data monitoring committee will consist of the principal investigator, a statistician, an EMDR therapy expert unaffiliated with this trial, and a patient representative with lived experience of depression. The committee will function under a formal charter that clearly defines its mandate. Its responsibilities include:Conducting quarterly blinded reviews of adverse event reports and unblinded interim efficacy analyses in accordance with O’Brien–Fleming boundaries.Evaluating protocol deviations that may affect data integrity.Issuing recommendations regarding trial continuation, modification, or termination based on safety and efficacy considerations.

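### The safety interim analysis commits the trial to one response to an excess of harm in an arm, carrying on with added sessions, and the stated plan does not link its by-arm result to the data monitoring committee's power to recommend stopping

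*Protocol article*

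**What the plan says.** Interim analyses {21b} plans two looks.

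- **First look (safety).** It takes place once 40 participants have completed mid-treatment assessment. "This evaluation will systematically compare adverse event profiles between the online and in-person EMDR groups", with attention to dissociation. If either arm shows substantially more events, "the protocol will be adaptively modified to incorporate additional stabilization sessions for affected participants while maintaining trial continuity". The section names no body that receives this result.
- **Second look (efficacy and futility).** It takes place when 60 participants have completed end-of-treatment evaluation. Here stopping is named twice: on success, "the trial could be responsibly terminated early based on established efficacy"; on a poor outlook for non-inferiority, "the futility provisions would be activated to conserve resources".

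The data monitoring committee section {21a} lists the committee's tasks. One is "Conducting quarterly blinded reviews of adverse event reports and unblinded interim efficacy analyses". Another is "Issuing recommendations regarding trial continuation, modification, or termination based on safety and efficacy considerations". On membership it says: "The Independent data monitoring committee will consist of the principal investigator", followed by a statistician, an EMDR expert from outside the trial and a patient representative.

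**The concern.** A substantial excess of harm in one delivery mode is the finding most likely to call for a pause or a stop. The protocol does not leave the response open. It states what will be done, and that response keeps the trial running.

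The committee that may recommend termination for safety is described as reviewing adverse events blinded. Unblinding is mentioned only for efficacy. If staff followed the text literally, they could meet a clear by-arm imbalance with extra sessions without the result reaching that committee in a form it could act on. At stake is the protection of participants. They enter with HAM-D-17 scores of at least 20, and section {11b} itself anticipates dissociation and suicidal ideation among them.

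**Working it through.** The concern rests on no planned figure, so the check compares the sections.

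**1. Timing.** First look: 40/80 = 50% of the target sample. Second look: 60/80 = 75%, as the protocol states.

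**2. Is there another between-arm safety comparison?** None was found. The other safety text covers:
- phase two, which has a single group;
- a perceived-safety scale for online EMDR, under Secondary outcomes;
- pausing therapy for an individual client, in {11b};
- event recording and reporting to the principal investigator, in {22};
- general safety oversight by independent steering committee members, under Oversight and monitoring.

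None of these compares the arms or mentions the first interim result.

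**3. What does {21b} prescribe?** For the first look: modify and continue. For the second: stop for efficacy or stop for futility. The example of raised dissociation in the online arm illustrates the kind of excess. It does not offer the response as one option among several.

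**4. What does {21a} give the committee?** It has two review streams: adverse events, blinded and quarterly; and efficacy, unblinded at the interim. The by-arm safety look is listed in neither. The power to recommend termination on safety grounds is stated separately and is not tied to that look.

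**5. What could blinded mean here?** Section {21a} does not define it.
- *Group codes.* This is the usage in section {17a}: "Data analysts will work with de-identified datasets using group codes". The committee could see an imbalance but not which delivery mode carries it.
- *Pooled data.* The committee could not see the imbalance. With assumed counts, 8 participants with dissociation out of 40 fits 4 of 20 against 4 of 20 (Fisher exact p = 1.00). It fits equally well 8 of 20 against 0 of 20 (two-sided p = 2 × C(20,8)/C(40,8) = 2 × 125,970/76,904,685 = 0.003). These counts only illustrate the pooled reading and are not from the documents.

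Under both readings, the listed quarterly review does not give the committee the identified by-arm comparison that {21b} produces.

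**6. Do other safeguards make the link?** The individual pause in {11b} is not a trial-level rule. Under {25}, major changes affecting participant safety need ethics approval before they are put into practice. That covers the amendment adding sessions, but the section does not say that the by-arm comparison accompanies it.

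**The case against.** The strongest reply is that the two sections can be read together: {21b} gives a default operational response, and {21a} gives the committee power to override it. The committee and the steering committee both work under charters that are not shown. An article commonly leaves the routing of interim tables to such documents. The blinded reviews are the quarterly ones, and nothing says that the separate safety look is withheld. Adding sessions would also need ethics approval first, and independent steering committee members oversee safety.

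Much of this stands, and it rules out several stronger readings that a reader might infer:

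- *That the trial cannot be stopped for safety.* Section {21a} expressly allows a recommendation to terminate on safety grounds. Counting the stopping routes within {21b} alone would miss this.
- *That added sessions could begin before any independent body is involved.* Section {25} requires ethics approval first.
- *That the committee is barred from the by-arm result.* Its charter may send it there, and blinded may mean coded groups.
- *That extra sessions would be offered unevenly.* The text already refers to either arm and to affected participants, so no defect is shown there.

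What the reply does not remove is the wording itself. If {21b} were merely silent on the response and its routing, leaving both to a charter would be fair. Instead it states a single response and commits to continuing. Section {21a} for its part states that adverse event review is blinded and mentions unblinding only for efficacy. A charter that sent this look unblinded to the committee, with the option to stop, would have to depart from that published text.

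**Conclusion.** The point holds as a modest flaw in patient-safety governance, and it should be corrected. The stated plan fixes one response to a substantial by-arm excess of adverse events. It does not link that result to the committee's power to recommend a stop.

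The documents support no numerical estimate of harm or bias, and nothing here bears on the HAM-D-17 comparison. The conclusion assumes that the first look would be run as {21b} describes and that the charters, which are not shown, do not already override it. If they do, the correction is one of wording only. Confidence is medium for that reason.

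**What to change.** 1. **Interim analyses {21b}.** Delete the closing clause of the response sentence, which commits the trial to carry on. State instead that the by-arm adverse event comparison goes to the data monitoring committee. Its members other than the principal investigator review it in closed session and may recommend continuing, modifying, pausing or terminating. Added stabilization sessions remain available as one possible modification.
2. **Data monitoring committee {21a}.** Add this unblinded safety look to the listed tasks, beside the blinded quarterly reviews.

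Ethics approval under {25} would then follow the committee's recommendation.

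The cost is a few sentences in two sections and matching wording in the committee charter. No new committee, visit, data item or change in sample size is needed. The downside is a possible short pause while the committee reviews the result.

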### Clients selection and sample size {14}

The study focuses on individuals with MDD in Pakistan, specifically selecting geographically accessible participants residing in the major cities of Rawalpindi, Islamabad, and Peshawar. Recent literature cites various studies such as by Ishtiaq et al. [56], Noor et al. [57] and Umar et al. [58] on the high prevalence of depressive disorders in these three cities of Pakistan. However, since the exact number of MDD cases in these three major cities is unknown, a more customized, multi-stage sampling procedure has been adopted.

Initially, three rehabilitation centers located in the selected cities will be randomly but purposively picked for recruiting patients. The centers will not be chosen fully at random; rather, the characteristics of the vicinity and patient flow into centers will be considered. Within each selected center, clients will be recruited using a sequential consecutive sampling technique with a rolling enrollment strategy. This approach involves selecting every eligible patient who meets the inclusion criteria until the required sample size is achieved [59]. The estimated sample size of (*n* = 80) was calculated by using the below given approximation method for two independent group means, as recommended in the existing literature by Sakpal [60] and Chow [61]:$$n=\frac{\left({Z}_{\frac{\alpha }{2}}+{Z}_{\beta }{)}^{2}\cdot (2{\sigma }^{2}\right)}{\left({M}_{1}-{M}_{2}{)}^{2}\right.}$$where.

*n*= is the estimated sample size.

Zα/2 = is the Z-score matching to the desired α level (for e.g., 1.96 for 95% confidence).

Z*β* = is the Z-score matching the desired power level (for e.g., 0.84 for 80% power).

σ^2^ = is the pooled variance of two groups.

µ​_1_ - µ​_2_= are the expected difference in means of depression scores.

A two-sided significance level of α = 0.05 was selected, consistent with conventional recommendations for clinical trials, resulting in α/2 = 0.025 and a corresponding Z-score of 1.96. Statistical power was set at 80% (1 − β = 0.80), yielding β = 0.20 and a corresponding Z-score of 0.84.

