Based on previously published depression trials utilizing the Hamilton Depression Rating Scale-17 [62], a pooled standard deviation (σ = 8 points, variance = 64) for change scores was assumed. An expected mean difference of five points of the scale between the two treatment groups was specified, representing a clinically meaningful difference in depressive symptom severity. Substituting these values into the formula:$$n=\frac{\left(1.96+0.84{)}^{2}\times (2\times {8}^{2}\right)}{{5}^{2}}$$$$n=\frac{7.84\times 128}{25}$$$$n=40$$

Hence, the estimated sample size required was 40 clients per treatment arm, resulting in a total sample size of 80 clients. Furthermore, to account for potential attrition, a dropout rate of 15% was assumed, consistent with longitudinal psychotherapy trials. The adjusted recruitment target was calculated using the formula:$${n}_{\mathrm{initial}}=\frac{{n}_{\mathrm{target}}}{1-r}$$$${n}_{\mathrm{initial}}=\frac{80}{0.85}=94$$

Accordingly, approximately 94 clients will be recruited to ensure that at least 80 participants complete the trial and are available for primary analysis.

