## Statistical methods

### Statistical methods for primary and secondary outcomes {20a}

All quantitative analyses in Phase two and Phase three will be conducted using appropriate statistical methods aligned with the study design, outcome structure, and hypotheses. Analyses will be performed using standard statistical software (e.g., SPSS and Python 3.10+, standard statistical libraries). Phase two analyses will focus on feasibility, acceptability, safety, and preliminary symptoms change following delivery of the culturally adapted DeprEnd EMDR protocol. Feasibility indicators will be summarized using descriptive statistics, and a one-sample t-test with 95% confidence intervals and significance levels. Repeated-measures General Linear Models will be used to determine temporal symptoms changes. These analyses will be exploratory and will not be intended to establish definitive clinical effectiveness.

Phase three analyses will be conducted within a randomized controlled trial framework. First, non-inferiority is evaluated by comparing the estimated 95% confidence interval for the between-group difference to a pre-specified margin; if the upper bound lies entirely below the margin, non-inferiority is concluded [81]. For the primary outcome, non-inferiority is based on the between-group difference in change scores on the Hamilton Depression Rating Scale-17 from baseline (T1) to the end of treatment (T3), calculated as online EMDR minus in-person EMDR. A non-inferiority margin (δ) of 3 points was pre-specified a priori, consistent with previously published non-inferiority trials that defined margins on this scale [82]. For secondary outcomes of anxiety, as assessed by the Generalized Anxiety Disorder-7, between-group differences in change scores will be examined using analogous comparative principles and reported with effect estimates and confidence intervals. A non-inferiority margin (δ) of approximately 2.5 points on this scale was pre-specified a priori, informed by clinically meaningful score differences used in prior non-inferiority psychotherapy trials [83].

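### The illustrated efficacy stop (0.5-point difference, p = 0.005, 60 completers) is incompatible with the planning SD of 8 and with the 3-point non-inferiority rule, and should be replaced by a criterion tied to the margin

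*Protocol article*

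**What the plan says.** Four parts of the protocol article bear on this.

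- **Interim analyses {21b}.** A second interim for efficacy and futility takes place at 60 end-of-treatment completers, 75% of the target, using O'Brien-Fleming boundaries. An efficacy stop is illustrated by online delivery coming close to in-person delivery, "as might be evidenced by merely a 0.5-point difference on the HAM-D-17 scale", with p = 0.005. The efficacy example names neither the null hypothesis behind that p-value nor the 3-point margin. The futility sentence does refer to non-inferiority.
- **Statistical methods for primary and secondary outcomes {20a}.** The primary comparison is the HAM-D-17 change from T1 to T3, online minus in-person, with a margin of 3 points and a 95% confidence interval: "if the upper bound lies entirely below the margin, non-inferiority is concluded".
- **Clients selection and sample size {14}.** For HAM-D-17, "a pooled standard deviation (σ = 8 points, variance = 64) for change scores was assumed".
- **Composition of the data monitoring committee {21a}.** The committee reviews unblinded interim efficacy against O'Brien-Fleming boundaries under a charter.

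**The concern.** The example treats a small observed difference as the evidence for stopping. Non-inferiority is not shown by a small point estimate. It is shown by an interval that excludes a loss of 3 points or more, and with about 30 clients per arm and an SD of 8 the interval is wide.

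The attached p-value adds to the difficulty. If it tests zero difference, a small value is evidence that the arms differ, which is the opposite of what the example is meant to show. If it tests the margin, a 0.5-point difference cannot give 0.005 at the planned SD.

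At stake is early termination on the trial's main claim. If the example were followed in its plain sense, the trial could be declared a success while the data still allowed online therapy to be more than 3 points worse.

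**Working it through.** **Inputs.** SD of change scores 8 and two-sided alpha 0.05 (section {14}); 1:1 allocation (section {16a}), so 60 completers are taken as 30 per arm; margin 3 and difference d = online minus in-person, positive when online is worse (section {20a}); interim at 60 of 80 (section {21b}).

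**The plan's own figures.** (1.96 + 0.84)² × 2 × 64 / 25 = 7.84 × 128 / 25 = 40.14, matching the stated 40 per arm; 60/80 = 75%.

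**Precision at the interim.** SE = 8 × √(2/30) = 2.066. The 95% half-width is 1.96 × 2.066 = 4.05.

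**A 0.5-point difference at SD 8, 30 per arm**

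| | Online 0.5 worse (d = +0.5) | Online 0.5 better (d = -0.5) |
|---|---|---|
| 95% CI, d ± 4.05 | -3.55 to 4.55 | -4.55 to 3.55 |
| Test of zero, 0.5/2.066 = 0.24 | two-sided p = 0.81 | two-sided p = 0.81 |
| Margin test, (3 - d)/2.066 | z = 1.21, one-sided p = 0.113 | z = 1.69, one-sided p = 0.045 |
| Upper limit below 3? | no | no |

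To meet the 95% interval rule at this point, d must be below 3 - 4.05 = -1.05.

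**What p = 0.005 would require.** At SD 8, a two-sided p of 0.005 against zero corresponds to a difference of 2.807 × 2.066 = 5.8 points. With a difference of only 0.5, the SD would have to be:

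- test of zero, two-sided: SE = 0.5/2.807 = 0.178, SD = 0.178/√(2/30) = 0.69;
- margin test, one-sided, online worse: SE = 2.5/2.576 = 0.971, SD = 3.76;
- margin test, one-sided, online better: SE = 3.5/2.576 = 1.359, SD = 5.26.

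All are far from 8. If the true SD were 8, a sample SD of 5.26 or less has a probability of about 5 in 100,000.

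**If both figures did occur together, with online 0.5 worse.** The upper 95% limit would be 0.5 + 1.96 × 0.178 = 0.85 (p against zero) or 0.5 + 1.96 × 0.971 = 2.40 (one-sided p against the margin). Both are below 3.

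**O'Brien-Fleming stop on the non-inferiority statistic.** With two looks, one-sided 0.025 overall and 75% information, the first bound is z = 2.327 in the classical form and 2.340 with Lan-DeMets spending (one-sided p about 0.010, two-sided about 0.020). The difference needed is d ≤ 3 - 2.327 × 2.066 = -1.81 (-1.83 with spending). If the arms are truly equal, the chance of crossing is Φ(-1.81/2.066), about 0.19.

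**Size of the risk if the example were misread.** If any observed difference of +0.5 or lower led to a stop, and online were truly 3 points worse, the chance of stopping would be Φ((0.5 - 3)/2.066) = 0.113, against about 0.010 for the proper boundary.

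**The case against.** The strongest reply is that the example is only an illustration. The operative instruction is to use O'Brien-Fleming boundaries, and it appears both in the interim section and in the committee's remit. A committee applying them to the non-inferiority statistic would not stop at 0.5 points with an SD of 8. The design, margin and interval rule are stated elsewhere, and the exact interim statistic and boundary form usually belong in an analysis plan or charter, which are not shown. This stands in part: the example is not the only operational text on the stop, and a missing boundary formula is no defect of the article. It does not rescue the example, which the article itself states and which conflicts with its own SD and decision rule.

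Three stronger readings are tempting and are not supported.

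- A reader might infer that the example, taken whole, fails the non-inferiority rule. It does not: with online 0.5 worse, data that really gave p = 0.005 would have an upper limit of 0.85 or 2.40. What fails is 0.5 points at the planned SD.
- A reader might infer that the trial will stop wrongly. A result that cannot arise under the plan's assumptions triggers nothing by itself. The wrong stop depends on the committee acting on the point difference or on a test of zero.
- A reader might infer that 0.005 is a misstated boundary. The article gives it as an observed p-value, and it would cross the 75% boundary of about 0.020 two-sided.

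Two further points are fair. Covariate adjustment could reduce the SE, but reaching a one-sided p of 0.005 at d = +0.5 would take a multiple correlation of about 0.88 with the change score (√(1 - (3.76/8)²)), which the plan does not assume. And the shortfall is not only an interim matter: at 40 per arm the upper limits are 4.01 and 3.006, so a 0.5-point difference would still fail at the final analysis.

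**Conclusion.** The concern holds in a limited form. Under the plan's own SD and interim size, the efficacy-stop example cannot be reconciled with the sample-size assumptions or with the primary decision rule. This is so whether the p-value tests zero or the margin, whether it is one- or two-sided, and whichever arm is ahead. The example's wording makes closeness of the estimates the reason to stop and leaves out the margin.

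The harm is conditional. It follows if the stop is read from the small difference or from a p-value testing zero, and not if the boundary is applied to the margin test. The figures assume exactly 30 completers per arm, an unadjusted comparison, an SD of 8 and a normal approximation. Using t instead widens the interval slightly (upper limits 4.63 and 3.63) and changes nothing.

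**What to change.** Delete the 0.5-point, p = 0.005 example. State in its place that the interim efficacy test is of the 3-point margin, and that the trial may stop for efficacy only if the O'Brien-Fleming-adjusted upper confidence limit for online minus in-person is below 3. At 75% information this is about a two-sided 98% interval (z about 2.33), to be recomputed for the information actually available and the boundary form chosen.

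A sentence telling the committee that, at SD 8 and 30 per arm, this means online about 1.8 points better would help but is optional. The monitoring charter should carry the same wording.

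The cost is a text amendment: no added clients, no new data and no change to the final analysis. An efficacy stop will visibly be seen as unlikely (about 19% if the arms are equal). Recruitment is reported as under way, so the change should be in place before the interim is used.

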### Recruitment {15}

Clients will be recruited through professional therapeutic networks across participating cities. The principal investigator has conducted preliminary site visits to psychotherapy clinics in selected Pakistani capital cities to establish collaborations. Patient recruitment will follow a consecutive rolling enrollment strategy at each participating clinic. All prospective patients will undergo:An initial diagnostic interview for MDD symptomatology verification.Comprehensive eligibility assessment using study criteria.

Recruitment will continue sequentially until the target sample size (*n* = 80) is achieved, with an anticipated enrollment rate of 8–10 clients per month. Immediately following selection, participants will begin their allocated treatment (online or in-person EMDR). This consecutive enrollment and immediate treatment initiation process will be maintained consistently across all study sites until complete sample acquisition.

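### The interim section's example of an efficacy stop (0.5 points, p = 0.005) does not fit the plan's own SD and margin, and the final 95% interval is not reconciled with that look

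*Protocol article*

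**What the plan says.** The section Interim analyses {21b} sets two looks. The first is for safety. The second, for efficacy and futility, takes place when 60 clients (75% of the target of 80) have finished the end-of-treatment assessment, and it uses O'Brien–Fleming boundaries. The section gives one concrete picture of an efficacy stop: if the data showed "merely a 0.5-point difference on the HAM-D-17 scale (*p* = 0.005)—the trial could be responsibly terminated early based on established efficacy". It does not say which hypothesis the p-value tests or which arm the half point favours.

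The section Composition of the data monitoring committee {21a} repeats the method, giving the committee "unblinded interim efficacy analyses in accordance with O’Brien–Fleming boundaries".

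The section Statistical methods for primary and secondary outcomes {20a} judges non-inferiority at the end by "comparing the estimated 95% confidence interval for the between-group difference to a pre-specified margin". The difference is online minus in-person in HAM-D-17 change from baseline to end of treatment, and the margin is 3 points. This section does not mention the interim look.

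The section Clients selection and sample size {14} supplies the planning figures: "A two-sided significance level of α = 0.05 was selected" and "a pooled standard deviation (σ = 8 points, variance = 64) for change scores was assumed".

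**The concern.** An efficacy stop in a non-inferiority trial has to show that the margin is excluded with the stricter confidence that an early look demands. Two nearly equal means do not show this if the interval around their difference is wide. The example pairs a small difference with a small p-value as though the two went together. At this trial's planned precision they do not.

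The example is the only concrete description of an efficacy stop in the article, so a committee member may take it as a guide to what success looks like. The stop would also end the trial on its primary claim.

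A second, smaller matter is the final rule. Once some of the error rate has been spent at 75% of the data, a plain 95% interval at the end no longer holds the one-sided 2.5% level.

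**Working it through.** **Inputs.** SD of change scores 8, two-sided alpha 0.05, 40 per arm (sample-size section). Allocation 1:1 (Sequence generation {16a}). Margin 3 points and direction online minus in-person (statistical methods section). Look at 60 of 80 completers, so 30 per arm and an information fraction of 60/80 = 0.75 (interim section). An upper 95% limit compared with the margin is a one-sided test at 0.025. A positive difference is taken to mean that online does worse, as the upper-limit rule requires.

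**The plan's own figure.** n = (1.96 + 0.84)² × 2 × 8² / 5² = 7.84 × 128 / 25 = 40.1. This agrees with the stated 40 per arm and 80 in total, and 80/0.85 = 94.1 agrees with the stated 94.

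**Precision at the look.** SE = 8 × √(2/30) = 2.066. The 95% half-width is 1.96 × 2.066 = 4.05.

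**The example under each reading, at SD 8**

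| Reading of the 0.5 points | z | p | Upper 95% limit |
|---|---|---|---|
| Against online, non-inferiority test | (3 − 0.5)/2.066 = 1.21 | 0.113 one-sided | 4.5 |
| Favouring online, non-inferiority test | (3 + 0.5)/2.066 = 1.69 | 0.045 one-sided | 3.5 |
| Test of no difference | 0.5/2.066 = 0.24 | 0.81 two-sided | – |

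No reading gives p = 0.005, and both upper limits lie above the 3-point margin.

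**SD that p = 0.005 would need.** The implied SD is (3 − d)/(z × √(2/30)), where d is the observed difference.
- One-sided non-inferiority p (z = 2.576): 3.8 if the difference is against online, 5.3 if it favours online.
- Two-sided p: 3.4 and 4.8.
- Two-sided test of no difference: about 0.7.

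**Boundary at 75% information, one-sided 0.025**
- O'Brien–Fleming-type spending: 2 × [1 − Φ(2.2414/√0.75)] = 0.00965, so z = 2.34. The classical form gives z = 2.33 (one-sided p 0.0100).
- Observed difference needed at SD 8: 3 − 2.34 × 2.066 = −1.8 or lower.
- Largest SD at which 0.5 points would cross: 2.5/(2.34 × 0.2582) = 4.1 against online, and 3.5/(2.34 × 0.2582) = 5.8 favouring online.

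**Final analysis.** The correlation between the two looks is √0.75. The final critical value that restores 0.025 is 2.012 (2.015 in the classical form), which corresponds to an interval of about 95.6%. Keeping 1.96 at the end gives P(Z₁ > 2.34 or Z₂ > 1.96) = 0.0276 (0.0277 in the classical form).

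**The case against.** The stated rule is the O'Brien–Fleming boundary, and the 0.5-point sentence is only an illustration. A reader might infer that the trial stops whenever the observed difference is half a point or less, and might work out a false-stop rate for such a rule. The article sets no such rule, and under the boundary it names, a stop would require the interim limit to exclude the margin. That objection stands: the fault is in the example, not in the choice of boundary.

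A reader might also infer that a 0.5-point difference can never cross. That is too strong. The observed SD may be smaller than planned, and the example carries its own p-value. A one-sided non-inferiority p of 0.005 would be beyond the bound of about 0.0096. What stands is that this p-value cannot accompany 0.5 points at the only SD the plan gives.

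Numeric boundaries and an adjusted final critical value are often left to an analysis plan, and naming O'Brien–Fleming implies one. Their absence from the article is therefore no fault. The article does, however, fix the final interval at 95% in terms that take no account of the look, and the cost of that is small.

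Two further inferences do not hold. The committee section might be read as allowing quarterly efficacy looks, but the interim section fixes two analyses and only the second concerns efficacy. Accrual may be well advanced by the time of the look, but that bears on how useful the look is. It is not an error, and it gives no ground for requiring that the look be removed.

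**Conclusion.** The concern holds in a limited form, at moderate severity. The example of an efficacy stop contradicts the plan's own SD and margin whichever arm is favoured: one-sided p of 0.113 or 0.045 against the stated 0.005, and z of 1.21 or 1.69 against a bound of about 2.34. It also leaves the tested hypothesis and the direction undefined. The unadjusted final interval raises the one-sided error from 0.025 to about 0.0276.

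The first conclusion rests on an observed SD near 8, and it would change at an SD of about 4.1 or below (against online) or 5.8 or below (favouring online). Equal arms of 30 and normal approximations are assumed. Measuring information against the 94 to be recruited instead of 80 (fraction 0.64) raises the bound to between 2.50 and 2.57 and leaves the conclusion unchanged. The error figure gives no credit for futility stopping.

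**What to change.** In Interim analyses {21b}, remove the 0.5-point and p = 0.005 illustration. State the efficacy criterion directly: at 60 completers, the upper limit of the 98.1% confidence interval for online minus in-person HAM-D-17 change lies below 3 points (1 − 2 × 0.00965 = 0.981).

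In Statistical methods for primary and secondary outcomes {20a}, base the final non-inferiority conclusion on a 95.6% interval (z about 2.01) and refer to the interim look.

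The cost is a change of wording and a marginally wider final interval. With 40 per arm and SD 8, SE = 8 × √(2/40) = 1.789, so the half-width goes from 1.96 × 1.789 = 3.51 to 2.012 × 1.789 = 3.60, about 0.09 points. The change should be in place before any unblinded look.
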